### Data Management

Data management and analysis will take place at the Contemplative Studies Centre at the University of Melbourne. During the data collection phase, data from Qualtrics will be encrypted before being stored in their respective cloud-based storage databases. Access to these databases is gated so that entry is only permitted to users entering through the approved route. The research team will access the data via a secure site, which is accessed only using verified credentials, and the data will be stored on a longer-term basis on a password-protected University of Melbourne computer. Qualtrics will be responsible for data storage during the data collection phase. In addition, Unforgettable Research Services Pty Ltd will administer the storage of data on Amazon Web Services. Amazon uses a sophisticated identity management and permission infrastructure that includes rotating keys and encrypted communications. Deidentifiable data will be stored online in perpetuity in line with open science best practices. Storage of downloaded data will be the duty of the responsible researcher, [name]. Deidentifiable data will be used by the research team for all analyses.

### Statistical Methods

#### General Principles

The primary analysis will be undertaken on the primary outcome following the intention-to-treat approach [56]. The intention-to-treat analysis sample will consist of all randomized participants, assigning them to the arms they were randomized to independently of their subsequent behavior. An intention-to-treat approach was chosen for the primary analysis because the study’s main purpose is to test whether larger *prescribed* doses of mindfulness practice yield larger effects on well-being. Intention-to-treat analyses will also be conducted for all secondary outcomes. Additional secondary analyses will be conducted following the per-protocol approach for all outcome measures (ie, primary and secondary). For data collected at weekly increments between T0 and T1, measurement occasions will be nested within individual participants.

The comparisons of interest will be each intervention (10, 20, and 30 min) compared to one another and with the minimal dose for each outcome (mean difference and 95% CI).

#### Baseline Characteristics

Demographic and baseline variables of participant characteristics will be summarized descriptively and presented by intervention group (4-min active control and 10-, 20-, and 30-min active group). No statistical comparisons between groups will be made at baseline. Characteristics will be summarized using frequencies and percentages (based on the observed sample) for categorical variables, means and SDs for continuous variables, or medians and IQRs for nonnormally distributed continuous variables.

#### Effectiveness Analyses

A constrained longitudinal data analysis method [57] will be used to build the linear mixed-effects model estimating the effect of the interventions on the primary outcome. The model will incorporate study visit (T0 and T1) as a categorical variable, intervention (10, 20, and 30 min each vs the minimal dose), and intervention by study visit interaction as main effects. The model will assume a common baseline mean of the outcome across the 4 intervention groups and an unstructured variance-covariance among the repeated measurements.

Models analyzing secondary outcomes will incorporate study visit (T0, T0.5, and T1) and intervention (10, 20, and 30 min each vs the minimal dose) as categorical variables. Secondary continuous outcomes will be analyzed similarly to the primary outcome (ie, the constrained longitudinal data analysis described previously). Additional analyses will include follow-up assessments (ie, T2) in the model.

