### Outcomes

#### Overview

*Personality* will be measured on days 2 and 3 of the run-in period using the short form of the Big Five Inventory, a 30-item measure of personality across 5 domains: open-mindedness, conscientiousness, extraversion, agreeableness, and negative emotionality [32].

*Sleep* will be assessed on day 4 of the run-in period using a single item from the Sleep Quality Scale [33]: “During the past week, how would you rate your sleep quality overall?” (response options: *terrible*=1, *poor*=2-4, *fair*=5-7, *good*=7-9, and *excellent*=10).

*Motivations and expectancy* will be measured on day 4 of the run-in period using the following questions: (1) “How much benefit do you expect from this mindfulness meditation course?” (response options: not at all to very much), (2) “What is your main goal for completing this mindfulness meditation course?” (goal or motivation free-text field), (3) “How motivated are you by this goal?” (response options: not at all to very much), (4) “How much improvement or progress toward your goal do you expect from the course?” (response options: none at all to a great deal), and (5) “How confident are you that the amount of improvement or progress you indicated will occur?” (response options: not confident at all to extremely confident).

The outcome measures in the following paragraphs will be obtained at baseline (T0) and the midintervention (T0.5) and postintervention (T1) time points and after a 1-month follow-up period (T2) unless otherwise indicated.

*Psychological well-being (primary outcome)* will be assessed at T0, T1, and T2 using the Warwick-Edinburgh Mental Wellbeing Scale (WEMWBS) [34], which includes 14 positively worded items of mental well-being for the previous 2 weeks on a 5-point Likert scale from 1 (none of the time) to 5 (all of the time). The primary outcome measurement is at T1. Previous analyses of responsiveness to change analyses indicate that the WEMWBS detects individually meaningful improvement across a variety of mental health measures [35]. These analyses indicated an average SE of measurement over time of 2.69.

*Psychological distress (secondary outcome)* will be assessed at T0, T0.5, T1, and T2 using the Kessler Psychological Distress Scale [36], a 10-item self-report measure of psychological distress over the previous month, on a 5-point Likert scale from 1 (none of the time) to 5 (all of the time).

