### Sample Size

A meta-analysis of meditation apps [1] indicates a standardized mean difference (SMD) effect size of 0.29 (95% CI 0.14-0.45) for psychological well-being when comparing apps to controls. A more recent study [6] randomized participants to approximately 10 or 30 minutes of sitting or movement practice for 2 weeks. They estimated a difference in the effects on the WEMWBS between the sitting groups of short and long duration of SMD=0.2 to 0.25. To be conservative, we determined a target sample size with an SMD of 0.2.

On the basis of an SD in WEMWBS scores of 9.84 [55] and a within-individual correlation of 0.83 in repeated assessments of the WEMWBS [34], we would need a final sample size of 688 participants to achieve 80% power (at the 2-sided *P*=.02 significance level to correct for multiple comparisons between conditions) to detect a difference of 1.97 points (SMD=0.2) for each active condition (10, 20, and 30 min) compared to one another and with the minimal-dose condition. This would translate to approximately 172 participants per arm. These calculations were conducted using the *sampsi* package in Stata (StataCorp).

Meditation app studies indicate overall retention rates of approximately 60% for active mindfulness meditation interventions [1]. Given our use of a run-in period, the aim of which is to allow participants who are most likely to disengage to do so before randomization, we anticipate postrandomization retention rates approximating 80%. In total, we will then recruit on a rolling basis until we achieve the required sample size at randomization of 860.

We will aim to recruit the full sample by March 31, 2025. We will conduct an interim analysis at this stage if the sample is at <90% of the target. If the sample is at ≥90% of the target by March 31, 2025, recruitment will be terminated. If continued recruitment is necessary (ie, we recruit <90% of the sample by March 31, 2025), recruitment will continue until the target sample is reached or 6 months (from March 31, 2025) have elapsed (whichever occurs first). If an interim analysis is required, the team member who undertakes this analysis will not implement the final analysis (as they will need to be unblinded). Other members of the team will undertake the final analysis and will alter the arm designation in the analytic code to further blind results relative to the interim analysis.

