#### Efficacy Analyses

Analyses of all outcomes will also be conducted on a per-protocol basis to test the efficacy of different doses under “ideal” conditions of high compliance. The model will incorporate study visit (T0, T0.5, and T1; additional analyses will include T2) and intervention (10, 20, and 30 min each vs the minimal dose) as categorical variables. The per-protocol analysis sample will consist only of those participants who were compliant with the allocated intervention dose, excluding those who did not comply as opposed to reallocating them to an arm representing their actual dose. A “complier” will be defined by having reported session completion for >66.67% and <117% of sessions (100%=6 weekly sessions=24 sessions).

Estimation of effects in randomized controlled trials is known to be biased when there are variable rates of nonadherence to treatment [58]. To control for prerandomization factors that may influence nonadherence to the 10-, 20-, and 30-minute conditions, we will adjust for prerandomization confounders for the per-protocol analysis, such as personality traits (conscientiousness [59,60]), openness to experience [59,61], depressive symptoms [59,61], and motivations and expectations [60]. The method of inverse probability weighting will be used to control for confounding bias due to prerandomization factors [62]. A causal diagram will be drawn to determine a priori potential pre- and postrandomization confounders associated with being a complier [58].

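### As written, the per-protocol model has no visit-by-arm term, so its arm coefficient averages in the pre-treatment visit and is not the T1 effect

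*Protocol article*

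**What the plan says.** Under General Principles, the comparisons of interest are "each intervention (10, 20, and 30 min) compared to one another and with the minimal dose for each outcome (mean difference and 95% CI"). For the Warwick-Edinburgh scale (WEMWBS), the Outcomes overview adds: "The primary outcome measurement is at T1".

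The Effectiveness Analyses section covers the intention-to-treat models. "A constrained longitudinal data analysis method [57] will be used to build the linear mixed-effects model", with visit (T0 and T1), "intervention (10, 20, and 30 min each vs the minimal dose), and intervention by study visit interaction as main effects". It continues: "The model will assume a common baseline mean of the outcome across the 4 intervention groups". The secondary-outcome models are first described by visit and intervention alone, but the text then ties them back: "Secondary continuous outcomes will be analyzed similarly to the primary outcome (ie, the constrained longitudinal data analysis described previously").

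The Efficacy Analyses section covers the per-protocol models for all outcomes: "The model will incorporate study visit (T0, T0.5, and T1; additional analyses will include T2) and intervention", both categorical. It names no interaction, no baseline constraint and no link to the constrained model. The sample is restricted to participants whose reported session completion falls within a set range. Inverse probability weighting is planned on prerandomization factors. Those named are personality traits, depressive symptoms, and motivations and expectations. The list is open, and the baseline outcome score is not named in it.

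**The concern.** In a model with visit and arm but no interaction, the arm difference is forced to be the same at every visit. T0 is measured before randomization, when no treatment effect can exist. The single arm coefficient is therefore a weighted average of a zero baseline effect and the later effects, and it does not estimate the T1 mean difference.

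The per-protocol analysis is meant to show what each dose does under good compliance. A coefficient pulled toward zero by the baseline visit could be read as showing that dose matters little even among compliers, when the model has diluted the effect.

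Reading the sentence as shorthand for the constrained model raises a different question. A common baseline mean across arms is justified by randomization, but compliers are identified after it. The Strengths and Limitations section itself expects adherence to fall as dose rises, so compliers in different arms may differ at baseline.

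**Working it through.** **Inputs (Sample Size section).** "SD in WEMWBS scores of 9.84 [55] and a within-individual correlation of 0.83 in repeated assessments of the WEMWBS"; difference 1.97 points; two-sided level .02; 80% power; about 172 per arm; 688 in total; 860 at randomization.

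**Step 1: reproduce the plan's figure.** The change-score variance factor is 2(1 − 0.83) = 0.34. Then n per arm = 2 × (2.326 + 0.842)² × 9.84² × 0.34 / 1.97² ≈ 170.3, rounded up to 171, or 684 in total against the stated 688. Also 688 / 0.8 = 860. The factor for a constrained or baseline-adjusted analysis is 1 − 0.83² = 0.3111. It gives 156 per arm (624), which does not reproduce the plan.

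**Step 2: what the additive per-protocol model estimates.** With equal SDs and equal correlations, generalized least squares gives each visit the same weight for a visit-constant arm effect. Let the T1 difference be 1.97 and the T0 difference 0.

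| Visits in model | Assumed effect, as fraction of the T1 effect | Arm coefficient | Fraction of T1 effect |
|---|---|---|---|
| T0, T1 | 0, 1 | 0.985 | 50% |
| T0, T0.5, T1 | 0, 0.5, 1 | 0.985 | 50% |
| T0, T0.5, T1 | 0, 1, 1 | 1.313 | 67% |
| T0, T0.5, T1, T2 | 0, 0.5, 1, 1 | 1.231 | 62.5% |

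The T0/T1 row needs no assumption about time course, only equal SDs at the two visits. It is relevant because the Outcomes overview schedules the WEMWBS at T0, T1 and T2. The Abstract and the Efficacy Analyses section imply a T0.5 measurement as well, and these statements need reconciling.

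**Step 3: precision of that coefficient.** For T0 and T1, SE = 9.84 × √[(2/172) × (1 + 0.83)/2] = 1.015. At the .02 level, power = Φ(0.985/1.015 − 2.326) ≈ 8.8%. The three-visit rows have SE 0.999 and power of about 9% and 16%. The four-visit row has power of 13.9%. These figures borrow the primary level and 172 per arm, which is an upper bound for a complier set.

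**Step 4: the same contrast with visit-by-arm terms (172 per arm).**
- Free baseline means: SE = 9.84 × √(2 × 0.34/172) = 0.619; estimate 1.97; power 80.4%.
- Common baseline mean: SE = 9.84 × √(2 × 0.3111/172) = 0.592; estimate 1.97; power 84.2%.

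Step 4 also gives the two ways of coding the primary model. With T0 as the reference visit, a free arm main effect is the baseline difference between arms, which the stated constraint sets to zero. The term list and the constraint therefore conflict in wording, but under randomization both codings are unbiased for the T1 difference.

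**The case against.** The best defence is that the sentence is shorthand in a condensed article. The secondary-outcome text uses nearly the same phrasing, visit and intervention as categorical variables, and the next sentence makes clear that the constrained model is meant. The Efficacy Analyses section says the per-protocol analyses are done in addition, which can be read as the same models in another sample. It also recognizes that compliers are not a random subset, and plans weighting and a causal diagram.

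Part of this stands. The protocol does not prove that an additive model is intended, and the 50% to 67% range is conditional on that reading. But the section writes out its own model without the link that rescues the secondary-outcome text. Supplying the link by inference brings in a common-baseline assumption that randomization does not secure among compliers. Neither reading gives a settled T1 contrast.

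A reader might also infer that the primary analysis fails to deliver its contrast or loses planned power. The documents do not support that. The interaction is listed, the constrained method is named and the common baseline is stated. Active-versus-active differences follow as linear contrasts. The planned sample size already matches the less precise coding, so 80% power holds on either reading.

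**Conclusion.** The point holds for the per-protocol analysis. Taken as written, the arm coefficient recovers 50% of a T1 difference with T0 and T1 only (equal SDs), and about 50% to 67% with T0.5 included. The latter range rests on assumed time courses and a correlation of 0.83 between all visits. If the constrained model is meant, no size can be given, because the protocol does not project how complier baselines will differ between arms; the point is only that equality is not assured.

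The primary model has a minor wording inconsistency. Coding a free arm main effect leaves the T1 contrast unbiased and gives power of about 80% instead of 84% at the protocol's correlation. The per-protocol analysis is secondary, so the main conclusion of the trial is not affected.

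**What to change.** In Efficacy Analyses:
- add visit-by-intervention terms;
- name the inverse-probability-weighted T1 contrast as the estimate;
- let baseline means differ by arm, or adjust for the baseline outcome and include it in the weights.

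The two baseline options rest on different assumptions: parallel change across arms for the first, and no remaining confounding once baseline and the weights are accounted for in the second. One should be fixed before unblinding.

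In Effectiveness Analyses, as a wording correction, drop the intervention main effect. The fixed effects are then visit plus arm at post-baseline visits, which matches the stated constraint.

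The cost is a few sentences. In the per-protocol analysis, free baseline means give slightly lower precision than a common-baseline constraint: SE 0.619 against 0.592 at 172 per arm, a ratio of about 1.05.

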#### Efficacy Analyses

Analyses of all outcomes will also be conducted on a per-protocol basis to test the efficacy of different doses under “ideal” conditions of high compliance. The model will incorporate study visit (T0, T0.5, and T1; additional analyses will include T2) and intervention (10, 20, and 30 min each vs the minimal dose) as categorical variables. The per-protocol analysis sample will consist only of those participants who were compliant with the allocated intervention dose, excluding those who did not comply as opposed to reallocating them to an arm representing their actual dose. A “complier” will be defined by having reported session completion for >66.67% and <117% of sessions (100%=6 weekly sessions=24 sessions).

Estimation of effects in randomized controlled trials is known to be biased when there are variable rates of nonadherence to treatment [58]. To control for prerandomization factors that may influence nonadherence to the 10-, 20-, and 30-minute conditions, we will adjust for prerandomization confounders for the per-protocol analysis, such as personality traits (conscientiousness [59,60]), openness to experience [59,61], depressive symptoms [59,61], and motivations and expectations [60]. The method of inverse probability weighting will be used to control for confounding bias due to prerandomization factors [62]. A causal diagram will be drawn to determine a priori potential pre- and postrandomization confounders associated with being a complier [58].

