### Interventions

#### Active Condition With Varied Doses

This study will include 3 active conditions that are dose variants of a newly developed 28-day mindfulness meditation program. The program is based on the *Satipatthana Sutta* (*The Discourse on the Establishing of Mindfulness* [28]—a foundational text within the Vipassana or insight tradition of Theravada Buddhism on which MBPs such as mindfulness-based stress reduction are largely based [29]). Most empirical work in the field of meditation has been conducted in the context of MBPs. The program generally aligns with the definition of an MBP developed by Crane et al [30]. The *Satipatthana Sutta* is structured into 4 progressive “contemplations”: body, feelings, mind, and “dhammas” or mental qualities [28]. This program will feature daily instructions and guided practices that are based on the first 3 contemplations: the body, feelings, and the mind.

The program has been developed independently by Australian meditation teacher [name] with support from Australian meditation teacher [name] based on specifications (ie, number of sessions, session length and duration, and intended audience) but with limited additional input from the research team. [name] has practiced meditation within the insight tradition since 1977 and has been teaching meditation full time for the past 20 years.

All 3 variants of the program will feature the same structure, progression, and content but will vary in length of daily teaching and practice: 10, 20, and 30 minutes. Each program consists of an introduction, practice, and conclusion. While the introduction and conclusion are consistent across the 3 programs, longer sessions include more practice points. Additional practice points in the longer sessions represent elaborations on content already introduced rather than new themes. In total, each 10-minute session includes 5 practice points, each 20-minute session includes 10 practice points, and each 30-minute session includes 15 practice points. The proportion of time allocated to spoken content varies across the 3 programs accordingly, from 62% for the 10-minute sessions to 47% for the 20-minute sessions and 40% for the 30-minute sessions.

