Practices will be provided for 6 days each week (ie, a total of 24 guided practices), with participants given the option to practice without guidance on the seventh day. Each variant will teach the same core content; however, the longer variants will have more time to elaborate on this content through teaching and gain experience practicing the guided techniques.

Practice instructions will consist of a brief explanation of relevant theory as well as a set of instructions for the practice in the first few minutes, followed by intermittent guided instructions throughout the duration of the practice. The programs will consist entirely of prerecorded material and will be delivered asynchronously. Therefore, there will be no direct contact between teachers and participants for the duration of the program. While this element constitutes a point of departure from how most MBPs are delivered, Crane et al [30] note that the exact method of delivery is flexible and can vary across MBPs [31].

After the 28-day intervention period, participants will be offered full access to any of the 3 higher-dose courses that they choose. During this time, participants will be free to choose to engage as much or as little with the guided practices as they wish.

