#### Weekly Measures

During the intervention period, additional measures will be obtained weekly (ie, 7, 14, 21, and 28 days after the baseline survey).

*Mindfulness* practice will be assessed using the following items: (1) “In the past week, how many daily sessions of this study’s meditation program did you complete?” (response options: 0-7); (2) “In the past week, on the days you meditated with the study program, approximately how many minutes (on average) was each meditation session?”; (3) “In the past week, how many additional days did you practice meditation?” (response options: 0-7) and “In the past week, on the days you meditated in addition to the study program, approximately how many minutes (on average) was each meditation session?”; (4) “On the days you practised meditation, how many minutes per session did you practice? (this includes the guided sessions in the meditation program)” (response options: 0 to ≥60 min); and (5) “In the past week, how often did you engage in informal mindfulness practice? i.e. mindfully washing dishes, showering, walking etc.” (response options: none of the time to all of the time).

*Adverse events* will be assessed using a modified short form of the Meditation-Related Adverse Effects Scale [50].

*Sleep* will be assessed using a single item from the Sleep Quality Scale [33]: “During the past week, how would you rate your sleep quality overall?” (response options: *terrible*=1, *poor*=2-4, *fair*=5-7, good=7-9, and *excellent*=10).

*Expectancy* will be assessed using the following item: “How effective do you think your training so far has been for your [goal or motivation free-text field from run-in survey]?” (response options: not at all effective to very effective).

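### The per-protocol complier rule counts sessions, which are the same in every arm, and ignores minutes, which are the randomised dose; its upper limit excludes nobody

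*Protocol article*

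**What the plan says.** All references are to the protocol article.

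- **Purpose.** Efficacy Analyses says the per-protocol analyses are "to test the efficacy of different doses under “ideal” conditions of high compliance". It adds: "The per-protocol analysis sample will consist only of those participants who were compliant with the allocated intervention dose".
- **Rule.** A complier is then "defined by having reported session completion for >66.67% and <117% of sessions (100%=6 weekly sessions=24 sessions"). No criterion on minutes stands beside it.
- **What differs between arms.** Under Active Condition With Varied Doses, the three programmes share structure and content but "will vary in length of daily teaching and practice: 10, 20, and 30 minutes". The schedule is common: "Practices will be provided for 6 days each week (ie, a total of 24 guided practices"), with an optional unguided seventh day. Minimal-Dose Control Condition describes sessions of about 4 minutes on the same course structure.
- **What is collected.** The first item under Weekly Measures asks for the number of programme sessions completed, from 0 to 7. Another asks, for days with the study programme, "approximately how many minutes (on average) was each meditation session". A further pair covers practice outside it: "In the past week, on the days you meditated in addition to the study program".
- **Where practice time is used.** Additional Analyses puts estimated practice time into a receiver operating characteristic analysis. It does not enter the complier rule.

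**The concern.** The rule measures something the arms have in common and leaves out the quantity that was randomised. Two kinds of departure from the allocated dose pass through it. Someone in a longer arm may stop sessions early and still report them as completed. Someone in a shorter arm may add practice of their own. Both bring actual minutes closer together across arms among people labelled compliant.

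The first is not far-fetched. Objectives hypothesises lower engagement at higher doses, and Strengths and Limitations expects lower adherence there. If some of that takes the form of shortened sessions, the rule cannot see it, and it falls mainly on the longer arms.

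At stake are the per-protocol contrasts, which are planned for every primary and secondary outcome. A null per-protocol result could then reflect similar minutes in practice and be read as evidence that dose does not matter under good compliance.

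**Working it through.** **1. The window in sessions.** Inputs: limits of 66.67% and 117%, and 24 sessions (Efficacy Analyses).

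- Lower: 0.6667 × 24 = 16.0008, so the smallest qualifying count is 17 (17/24 = 70.8%).
- Upper: 1.17 × 24 = 28.08, so the largest is 28.

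**2. Can the upper limit exclude anyone?** The weekly item runs from 0 to 7 and is asked four times, so the maximum is 4 × 7 = 28 and 28/24 = 116.67%, below 117%. No possible answer pattern breaches the limit. This takes the weekly item as the source; the article does not name the source, but this is the only session-count question it describes. Additional practice is asked separately and does not enter the count.

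**3. The window in minutes.** Sessions × session length, if every session is taken in full:

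| Arm | Allocated (24 sessions) | Complier range (17 to 28 sessions) |
|---|---|---|
| 4 min | 96 | 68–112 |
| 10 min | 240 | 170–280 |
| 20 min | 480 | 340–560 |
| 30 min | 720 | 510–840 |

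A 30-minute participant averaging 10 minutes logs 17 × 10 = 170 to 28 × 10 = 280 minutes. That is 170/720 = 24% to 280/720 = 39% of the allocation, and it equals the 10-minute complier range. This participant is a complier.

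**4. Effect on a contrast.** Assume an effect linear in minutes and equal session counts. Let a share f of 30-minute compliers practise 10 minutes per session.

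- Mean minutes in the 30-minute arm: 30 − 20f.
- Share of the 30-versus-10 contrast retained: (30 − 20f − 10)/20 = 1 − f.
- f = 10% gives 90%; f = 25% gives 75%; f = 50% gives 50%.
- At f = 50% the mean is 20 minutes, the same as the 20-minute arm.

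If in addition a share g of 10-minute compliers bring themselves to 30 minutes per day, the retained share is (30 − 20f − 10 − 20g)/20 = 1 − f − g. The protocol gives neither f nor g, so these are illustrations over a range.

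**5. Would the same percentage band on total minutes work?** In the 4-minute arm the ceiling would be 96 × 28/24 = 112 minutes.

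- An adherent control who rounds 4 to 5 minutes reports 24 × 5 = 120 minutes (125%) and is dropped.
- Four optional seventh-day practices of 5 minutes give 96 + 20 = 116 minutes, also over.
- The 30-minute arm has 840 − 720 = 120 minutes of headroom, against 112 − 96 = 16 in the control arm.

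A plain total-minutes band would therefore remove correctly behaving controls selectively.

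**The case against.** The best defence is that the rule counts completed sessions. The sessions are prerecorded and of fixed length within each arm, so completing a 30-minute session ordinarily takes about 30 minutes. Participants are also asked not to practise beyond the programme. The per-protocol analyses are secondary, the authors concede that uneven adherence may limit what these analyses can show, and practice time is examined elsewhere.

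Much of this stands. The word completed gives some protection, and nothing in the protocol shows how often shortened sessions would be reported as completed. The primary analysis, defined under General Principles by prescribed dose, is not touched.

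It does not remove the mismatch. No minimum length defines completion, and the survey asks separately for minutes, which implies that length can vary. The request to avoid further practice is not enforced by the complier rule. The authors' concession is about adherence in general and does not address session length. The planned inverse probability weighting does not help either: it adjusts for prerandomisation factors related to being a complier, with complier defined by the same session count.

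A reader might infer that the per-protocol comparison loses its meaning or could change direction. The protocol does not support that. Under the linear illustration, reversal of the 30-versus-10 contrast needs f + g above 1, and nothing in the text points to shares of that size. A reader might also think that rounding two thirds to 66.67% wrongly excludes 16 sessions. It does not: a strict limit of more than two thirds excludes 16 of 24 as well.

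**Conclusion.** The point holds as a mismatch between a stated aim and a stated rule in a secondary analysis. The set is described as "those participants who were compliant with the allocated intervention dose", but membership depends only on reporting 17 to 28 sessions, in every arm alike. Session length and additional practice play no part, and the upper limit is inoperative.

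The firm consequence is dilution in proportion to the share of misclassified compliers. The retained 30-versus-10 contrast is 1 − f, for example 75% at f = 25%. This rests on an effect linear in minutes, on equal session counts, and on shares that the protocol does not give; if nearly all reported sessions are full length and additional practice is rare, the loss is small. The inoperative ceiling follows from the weekly item alone and needs no such assumption. The intention-to-treat conclusions do not depend on any of this.

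**What to change.** Reconcile the complier rule with the allocated dose, before anyone sees unblinded data:

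1. Keep the session-count criterion, and write its lower limit as a number of sessions (17 under the present wording).
2. Add a requirement that the average reported minutes per programme session be close to the allocated length. The lower bound should lie above the next shorter arm's length. Two thirds of 30 is 20 minutes, so a two-thirds floor would not separate the 30- and 20-minute arms.
3. Add a limit on additional practice from the weekly items. State how the question on additional days is read, and allow for the optional seventh-day practice.
4. Give both new criteria a rounding tolerance in absolute minutes, so that a 4-minute participant who reports 5 is kept. Do not apply one percentage band to total minutes.
5. Remove the 117% limit, or let the limit on additional practice replace it.
6. Keep the session-count-only set as a sensitivity analysis.

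The cost is analysis wording, since the items are already collected weekly. The downsides are that self-reported minutes are noisy and that the per-protocol set becomes smaller.
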